#### Data collection for the implementation evaluation

Qualitative and quantitative data will be collected for the implementation evaluation. The development of testable realist initial programme theories will occur using data from the co-design, Theory of Change work, a document review, narrative review and informal discussions with international RHD active case finding experts. For the realist evaluation (table 2), the co-design process will inform what data will be collected and how, as well as outcome measures indicating successful implementation. Community-directed metrics of programme success may result in an expanded set of outcome measures. It is anticipated that data collection methods may include interviews, surveys, focus groups and observational field notes. All data collected in the NEARER SCAN study will also contribute to testing and refining the programme theories of the realist evaluation.

#### Qualitative data analysis

Qualitative data analysis will be conducted using a framework approach for the Theory of Change and a process of retroduction using abductive reasoning for the realist evaluation (ie, identifying the most likely explanation for each set of observations). Data will be organised using QSR NVivo V.12,^55^
^55^ stored on a secure server at Menzies School of Health Research (Darwin, Australia). These data will be mapped to different nodes within NVivo which will be grouped for each community involved in the study. The coding will be set up in a way to allow for identification of themes across communities.

#### Evaluation of clinical effectiveness

Clinical effectiveness of the intervention will be evaluated based on analysis of impact on key clinical outcome measures. The primary outcome for evaluation of clinical effectiveness is change in proportion of the target population prescribed secondary prophylaxis for RHD by the end of the study compared with a baseline timepoint prior to the date of echocardiographic active case finding (table 3).

**Table 3 T3:** Clinical effectiveness evaluation outcome measures

Outcome measure	Data collection	Data variables	Data analysis
**Primary outcome**			
Change in the proportion of the target population who are prescribed secondary prophylaxis based on national (Australia or Timor-Leste) RHD guidelines	Primary healthcare records Local RHD register	Initial BPG prescriptionInitial BPG delivery	Descriptive statisticsTwo-tailed comparison of proportions
**Secondary outcomes**			
Proportion of people with an abnormal or uninterpretable screening echocardiogram who get a full diagnostic echocardiogram within 3 months and receive a diagnosis	Primary healthcare records Local cardiology/echocardiography service provider records and primary healthcare records	Echocardiography referralEchocardiography completedCardiology review completedHealthcare worker interaction for diagnosis	Descriptive statistics
Proportion of people diagnosed with RHD who are retained in the cascade of care	Primary healthcare records Cardiology/specialist service provider records	GP interaction re RHD recordedSpecialist referral generatedSpecialist review completed	Descriptive statistics
Proportion of people prescribed secondary prophylaxis who receive ≥80% indicated doses in the 12 months prior to the end date of the study	Primary healthcare records Local RHD register	BPG prescriptionBPG delivery	Descriptive statistics
Description of antenatal and birthing care, and maternal and birth outcomes in women diagnosed with RHD on echocardiographic screening	Hospital and primary healthcare records	Location of deliveryMode of deliveryICU admissionNICU admissionPeripartum cardiovascular complication	Descriptive statistics
Prevalence of RHD and distribution of severity in children and pregnant women	Study database Primary healthcare records Local RHD register	Disease severity RHD diagnosis	Descriptive statistics

.BPG, benzathine penicillin G; GPgeneral practitionerICU, intensive care unit; NICU, neonatal intensive care unit; RHD, rheumatic heart disease

The primary outcome will be reported for all communities as well as aggregated results for Australia and Timor-Leste. This primary outcome represents a clinically meaningful outcome demonstrating whether active case finding for RHD results in a change in practice at the individual patient level that has a measurable public health impact in terms of increased access to guideline-based care. The proportion of the population prescribed secondary prophylaxis is expected to increase with detection of new RHD cases but may also be reduced as people complete treatment. The number of people in each community who are commenced on secondary prophylaxis and the number of people in each community who cease secondary prophylaxis during the study period will be collected as secondary outcomes. Other secondary outcomes include elements of the cascade of care from diagnosis to antibiotic adherence (online supplemental material (Cascade of Care).

This study will also report on maternal and birth outcomes in women found to have RHD on echocardiographic screening, and prevalence of RHD in screened populations (table 3).

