Evidence supporting a task-sharing approach in echocardiographic detection of RHD is derived from diagnostic accuracy studies conducted in endemic regions.^25^,^33^ Task-sharing refers to healthcare tasks being completed collaboratively by healthcare providers with different training.^34^ By contrast, task *shifting* differs in that the task is completely transferred to a different cadre of the workforce. Early studies of task *shifting* for echocardiographic detection involved nurses who were trained to perform echocardiography and interpret images.^26 30^ Our work to date in Australia and Timor-Leste has identified superior diagnostic accuracy with task-sharing, whereby an expert can review images obtained by a non-expert who has been trained to use a hand-held echocardiographic device to obtain images based on an abbreviated Single Parasternal Long Axis view with a Sweep of the Heart (SPLASH) protocol.^28 35^ The SPLASH protocol aligns with the 2023 WHF screening criteria for the echocardiographic diagnosis of RHD.^21^ We have been able to demonstrate acceptable diagnostic accuracy (sensitivity 76.7% (95% CI 68.5% to 83.7%), specificity 94.9% (95% CI 94.0% to 95.6%)) using this approach.^35^

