## Methods

### Study design

NEARER SCAN is a type II effectiveness-implementation hybrid study, evaluating implementation of an intervention designed to achieve early detection and management of RHD in high-risk populations. The study will run from August 2022 to June 2025. A package of implementation strategies will be co-designed at each site with the local community and participating primary healthcare service around non-adaptable elements of the intervention (table 1), and mapped onto an initial Theory of Change framework. Co-design, implementation and evaluation will occur simultaneously, and we will evaluate both the implementation strategy and the clinical effectiveness of the intervention.^36^

**Table 1 T1:** The non-adaptable functions of the active case finding programme and some of the adaptable forms of the active case finding programme to be locally tailored during the co-design process

Function (non-adaptable)	Form (adaptable)
Creating a community-led implementation group that provides feedback throughout the study	Size, membership and style of consultation with community-led implementation group (eg, meeting together or individual discussions)
Training local staff to acquire echocardiogram images	Who does the active case finding (eg, professional backgrounds of the staff trained, number of staff members trained)
Using Philips Lumify hand-held device	When the active case finding occurs (eg, annual check-ups, set days per month, community events)
Using defined SPLASH protocol	Where the active case finding occurs (eg, at the clinic, in school, house visits, outstations)
Cardiologists reviewing images	Defining what constitutes a successful programme at each site
Entering data into REDCap and cardiologists entering structured report into Tricefy	The implementation strategies to assist integration at each site
Linking positive screens into the cascade of care	

SPLASHSingle Parasternal Long Axis view with a Sweep of the Heart

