**Figure 2 F2:**
[figure not shown]
Non-Expert Acquisition and Remote Expert Review of Screening echocardiography images from Child health and AnteNatal clinics (NEARER SCAN) active case finding programme flow chart. *Abnormal SPLASH echocardiogram defined below. Diagnosis of RHD will be based on the revised World Heart Federation (WHF) minimum echocardiographic criteria for RHD. +If initial SPLASH is uninterpretable, educational and training feedback with be given to the non-expert by the expert reviewer. A repeat SPLASH will then be performed. If repeat SPLASH images are abnormal, or again not interpretable, the participant will be referred for a diagnostic echocardiogram. AHP, Aboriginal health practitioner; GP, general practitioner; RAN, remote area nurse; RHD, rheumatic heart disease; SPLASH, Single Parasternal Long Axis view with a Sweep of the Heart.

A SPLASH echocardiogram will be performed by a trained local healthcare worker using a Philips Lumify hand-held echocardiographic device. The SPLASH images will be uploaded to Tricefy, which is a cloud-based medical image communication application (California, USA). Images will be accompanied by identifiable participant data (name, date of birth, medical record number) and the local healthcare worker’s name. Healthcare workers will have the option to add a comment that includes their interpretation of the image findings, or other relevant clinical information. The uploaded images will then be reviewed and reported by an off-site cardiologist with expertise in RHD (referred to as an expert for study purposes) within 72 hours. The cardiologist will decide whether the images are normal, abnormal or uninterpretable according to the definitions in online supplemental material (Definitions of abnormal Single Parasternal Long Axis view with a Sweep of the Heart (SPLASH) echocardiogram),^21^ uploading their interpretation, recommendations and any additional notes in a report that will be accessible to healthcare staff on Tricefy.

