Additional mechanisms for push notification of SPLASH results will be developed with individual sites. These may include integration with existing electronic medical record systems, automated emails or use of secure phone messaging services such as WhatsApp or Signal. In addition, healthcare workers will be able to contact an on-call remote expert for discussion of SPLASH findings and advice regarding next steps. Non-experts will receive ongoing supervision and feedback from reviewing experts on image acquisition quality and image findings, and uninterpretable images will be reattempted. Participants with abnormal or repeated uninterpretable images should be referred by the local healthcare service for a full diagnostic echocardiogram.

Treatment decisions will usually be made following a full diagnostic echocardiogram and specialist review. If, however, the SPLASH findings are strongly suggestive of RHD, or there are other clinical indications for treatment, the primary healthcare team may choose to initiate counselling, treatment (including for suspected RHD) and/or additional referrals before completion of the full diagnostic echocardiogram.^51^

Any new case of RHD will be notified to the relevant local or jurisdictional RHD register, based on national guidelines in Australia and Timor-Leste.

Data audits will be conducted at least monthly, and if abnormal or uninterpretable SPLASH images have not been appropriately actioned, a reminder will be sent to the relevant healthcare service as a safety net in the context of this study. Referrals or treatment that occur as a result of these reminders will be evaluated separately to those that are generated as a result of the primary healthcare service response to the initial report.

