### Participation and recruitment

Eligible participants are children and young people aged 5–20 years residing in participating communities, and pregnant women at high risk for RHD. Pregnant women are considered to be at high risk if they are Aboriginal or Torres Strait Islander, or if they live in a remote community in northern Australia, or if they have immigrated to Australia from a high-prevalence country with all-age RHD prevalence >1 per 1000 people, or if they live in Timor-Leste. Women, children and young people with known history of ARF, RHD or other existing cardiac disease will not be excluded.

Pathways for recruiting eligible participants will be co-designed with each local community and participating primary healthcare service. We anticipate that this will primarily involve scanning opportunistically in the primary healthcare setting, with occasional organised screening days at local schools or community centres. In some settings, scanning may occasionally occur in the neighbourhoods as guided by trained local staff.

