#### Sample size calculation

The sample size has been calculated based on the primary outcome measure. To observe an absolute increase of 2.4% of the target population prescribed secondary prophylaxis, from a baseline prevalence of 4.4% to 6.8% (based on previous data from the Northern Territory^3^), with 95% two-sided significance and 80% power, the sample size required is 1421. However, if a lower proportion of the target population is prescribed secondary prophylaxis at baseline (as expected in Western Australia and Timor-Leste), then the power of the study is increased. The study will aim to enrol >1500 participants (children and pregnant women) across approximately 10 sites (~150 participants per site); five sites in Australia and five sites in Timor-Leste over 18 months.

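### The diagnostic-echocardiogram outcome in Table 3 counts as failures people whose uninterpretable first scan repeats as normal, whom the study's own pathway does not refer

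*Protocol article*

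**What the plan says.** Table 3 (Secondary outcomes) lists, for descriptive analysis: "Proportion of people with an abnormal or uninterpretable screening echocardiogram who get a full diagnostic echocardiogram within 3 months and receive a diagnosis".

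The referral rule appears twice under the heading on embedding SPLASH into healthcare delivery. The Figure 2 legend says that an uninterpretable first scan is repeated after feedback to the operator, and then: "If repeat SPLASH images are abnormal, or again not interpretable, the participant will be referred for a diagnostic echocardiogram". The text after the figure says: "Participants with abnormal or repeated uninterpretable images should be referred by the local healthcare service for a full diagnostic echocardiogram". Both set the referred group by the result after the repeat step.

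Table 3 also has an adherence outcome: "Proportion of people prescribed secondary prophylaxis who receive ≥80% indicated doses in the 12 months prior to the end date of the study". On timing, the Sample size calculation section plans "five sites in Australia and five sites in Timor-Leste over 18 months", and Study design states: "The study will run from August 2022 to June 2025". No date for the last scan is given.

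**The concern.** The table and the pathway describe different groups. The referral text covers repeated uninterpretable images; the Table 3 denominator drops that qualifier. Someone whose first scan is uninterpretable and whose repeat is normal has completed screening and is not referred. That person will have no diagnostic echocardiogram within 3 months, so the outcome records a linkage failure where none occurred.

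The error runs one way: it can only lower the reported proportion. It also depends on image acquisition. The scanners are newly trained local staff and the evaluation aims to explain differences between sites. A site with more unreadable first scans would look worse at linking people to diagnosis even if it linked every referred person equally well. Two separate implementation questions, image quality and referral completion, would be merged in one figure. This matters for the objective on clinical effectiveness, which includes linkage to guideline-based care.

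**Working it through.** The article states no expected value for this outcome, so there is no planned figure to reproduce. Its one sample size (1421, for 4.4% versus 6.8%) concerns the primary outcome. It is close to standard formulas (1425 by arcsine, 1440 pooled) and does not involve this denominator.

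**Who is in the denominator, and who is referred**

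| Path | In Table 3 denominator | Referred under pathway |
|---|---|---|
| First scan abnormal | yes | yes |
| First uninterpretable, repeat abnormal | yes | yes |
| First uninterpretable, repeat uninterpretable | yes | yes |
| First uninterpretable, repeat normal | yes | **no** |
| First uninterpretable, never repeated | yes | not yet; a real loss |

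The fourth row is the mismatch. The fifth is a true gap in care that any corrected measure should still show.

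**Inputs for an illustration**

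- Accuracy, from the Introduction: "sensitivity 76.7% (95% CI 68.5% to 83.7%), specificity 94.9% (95% CI 94.0% to 95.6"%).
- Prevalence 5%: the Introduction gives this as an upper figure for school-age children in some communities.
- u, share of first scans uninterpretable: not in the article; assumed 2%, 5%, 10%.
- f, share of repeats that are again uninterpretable: not in the article; assumed 10% and 30%.
- Perfect care: everyone is rescanned, and everyone referred completes.

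**Formulas**

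- Abnormal share of readable scans: a = 0.05 × 0.767 + 0.95 × 0.051 = 0.0868.
- Table 3 denominator, as a share of those scanned: D = (1 − u)a + u.
- Referred: R = (1 − u)a + u[f + (1 − f)a].
- Highest attainable value: R/D.

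For u = 5%: D = 0.95 × 0.0868 + 0.05 = 0.1325, or 199 per 1500. With f = 10%, R = 0.0825 + 0.05 × 0.1781 = 0.0914, or 137. With f = 30%, R = 0.0825 + 0.05 × 0.3608 = 0.1005, or 151.

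| u | D per 1500 | R per 1500 (f = 10% to 30%) | Ceiling R/D |
|---|---|---|---|
| 2% | 158 | 133 to 138 | 84% to 88% |
| 5% | 199 | 137 to 151 | 69% to 76% |
| 10% | 267 | 144 to 171 | 54% to 64% |

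At u = 5%, a true completion of 80% among those referred would be reported as 0.80 × 0.69 = 55% to 0.80 × 0.76 = 61%. For two sites that both complete 80% of referrals, with f = 10%, the one with u = 2% reports 0.80 × 0.84 = 67% and the one with u = 10% reports 0.80 × 0.54 = 43%.

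**Sensitivity to the assumptions.** A simpler form, (a + u(1 − r))/(a + u), where r is the share of uninterpretable scans that repeat as normal, was run with r from 50% to 90% and u from 2% to 10%. The ceiling runs from 91% down to 52% at 5% prevalence. At an assumed 2% prevalence (a = 0.0653) it runs from 88% down to 46%. The size moves a good deal; the direction does not.

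**The 3-month window.** With even accrual over 18 months and extraction on the day of the last scan, 3/18 = 17% of those scanned lack 3 months of observation. With a gap of 3 months or more the share is 0%.

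**The case against.** The strongest reply is that the table entry is a short label. The screening result could mean the final result after the repeat, in which case the mismatch disappears. The supplemental Cascade of Care, which is not shown, may say so. Referral and completion are listed as separate variables, and each cascade stage is to be reported with a 95% CI, so completion among those referred could be derived. The broad denominator also keeps people who were never rescanned.

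Part of this stands. The supplement could settle the wording, and the never-rescanned group must not be lost. But the article uses uninterpretable for the cardiologist's reading of a single set of images and adds a qualifier when it means the repeat. Table 3 has no such qualifier, and it is the stated definition. Being able to derive a better proportion does not change the one that is specified.

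Three stronger readings are tempting and are not supported:

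- **People who start prophylaxis late cannot meet the adherence outcome.** The outcome counts indicated doses. These can be read as doses due from the person's own start, so a late starter can reach 80%. What remains is that short and full histories are pooled, since "Women, children and young people with known history of ARF, RHD or other existing cardiac disease will not be excluded". Separating them is a refinement.
- **Late-screened people are necessarily failures on the 3-month outcome.** This needs scanning in the last 3 months before extraction. The article gives no last-scan date, and 18 months of enrolment within about 35 months of study leaves room for follow-up. A follow-up rule may also sit in the analysis plan.
- **Cascade performance is uninterpretable.** The outcomes are descriptive and the stages are reported separately. Biased downward, by an unknown amount, is as far as the text goes.

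**Conclusion.** The point holds for the denominator of the diagnostic-echocardiogram outcome. As worded, Table 3 does not match the referral pathway in the same article. Perfect care cannot score 100%, and the shortfall grows with first-scan image failure. This rests on the literal reading of Table 3. The direction needs only that some uninterpretable scans repeat as normal.

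The size is not known. The ceiling of about 54–88% is an illustration that depends on assumed uninterpretable and repeat-failure rates and on a prevalence at the top of the quoted range.

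The 3-month truncation is conditional on when scanning stops. The adherence outcome is not shown to be wrong. Both outcomes are secondary and descriptive, so no hypothesis test is affected, and neither is the primary outcome or its sample size. The change is worth making because the outcome is a main measure of linkage to care and the correction is cheap.

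**What to change.** 1. Define the denominator by final SPLASH result: abnormal (on the first or repeat scan), or uninterpretable on repeat. This takes the pathway as written. If a different referral rule is intended, the pathway text and Table 3 must be reconciled.
2. Report completion of the repeat SPLASH after a first uninterpretable scan as its own cascade step, so that people never rescanned stay visible.
3. If scanning continues into the last 3 months before data extraction, limit the 3-month proportion to people with 3 months of observation.
4. Optional: report adherence separately for people already prescribed prophylaxis at baseline and people newly started. On the planning figures, ignoring cessation, 4.4/6.8 = 65% of those prescribed at the end would have been prescribed at baseline, so a pooled figure would mostly describe them.

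The cost is a wording change in Table 3 and the analysis plan. The listed sources already cover expert SPLASH interpretations, referral, echocardiogram completion, prescription and delivery. The denominator shrinks (199 to 137–151 per 1500 in the 5% illustration) with little effect on precision. Ignoring clustering, the 95% half-width is 1.96 × √(0.80 × 0.20/137) = 6.7 points for 80% of 137, against 1.96 × √(0.55 × 0.45/199) = 6.9 points for 55% of 199.

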#### Sample size calculation

The sample size has been calculated based on the primary outcome measure. To observe an absolute increase of 2.4% of the target population prescribed secondary prophylaxis, from a baseline prevalence of 4.4% to 6.8% (based on previous data from the Northern Territory^3^), with 95% two-sided significance and 80% power, the sample size required is 1421. However, if a lower proportion of the target population is prescribed secondary prophylaxis at baseline (as expected in Western Australia and Timor-Leste), then the power of the study is increased. The study will aim to enrol >1500 participants (children and pregnant women) across approximately 10 sites (~150 participants per site); five sites in Australia and five sites in Timor-Leste over 18 months.

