**Methods and analysis:**

Echocardiograms will be obtained by trained local staff using hand-held echocardiographic devices employing the ‘Single Parasternal Long Axis view with a Sweep of the Heart’ (SPLASH) technique and interpreted by experts remote from the site of acquisition. Approximately 1500 children and pregnant women will be screened across high-risk communities in Australia and Timor-Leste over an 18-month period. The study will use a type II effectiveness-implementation hybrid design. A tailored package of implementation strategies will be co-designed with communities and health services and mapped onto a Theory of Change framework. The clinical effectiveness will be assessed as the change in the proportion of the target population that are prescribed secondary prophylaxis for RHD by the end of the study compared with baseline. The implementation will be assessed as the adoption, penetration, sustainability, fidelity and cost of the programme with a mixed-methods theory-based and economic evaluation. Data will include numbers of normal, abnormal and uninterpretable SPLASH echocardiograms obtained, numbers of participants progressing through the cascade of care, interviews with staff and programme costs.

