### Setting and population

The study will be carried out in approximately 10 primary healthcare and antenatal care settings across Timor-Leste and Australia’s Northern Territory and Western Australia. Stakeholder engagement and discussions underpinning the approaches to be used in this study have occurred over several years at participating sites in Australia and Timor-Leste. Community members have identified RHD as a significant priority and have sought out initiatives targeting early case detection and management. Extensive consultations have resulted in requests to transition echocardiographic detection from isolated research activities into implementation of a co-designed RHD active case finding programme within communities.

The target population in each community includes children and young people aged 5–20 years and pregnant women, representing high-risk subpopulations for RHD. In these culturally and linguistically diverse settings, native language speakers, interpreters and training and community health promotion materials in local languages will be used, relevant to each site.

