#### Quantitative data analysis

Quantitative analysis of clinical effectiveness data will be conducted using STATA V.18 (StataCorp, USA). The proportion of the target population prescribed secondary prophylaxis will be calculated prior to recruitment and screening participants, and at completion of the study, and will be described with 95% CIs. Numerator data will be obtained from clinic and RHD register data; the denominator will be based on census population data or health information system population data, following consultation with the community-led implementation group regarding the most accurate source for local population estimates.

The absolute change in proportion of the target population prescribed prophylaxis will be calculated with adjustment for clustering by community and described with 95% CIs. Proportions from commencement and completion of the study will be compared using a two-tailed comparison of proportions test. A p value <0.05 will be considered significant.

Descriptive analyses will be used to quantify secondary outcomes on the epidemiology of RHD in the target population at completion of the study. The proportion of enrolled participants progressing through each stage of the RHD cascade of care will be calculated (with 95% CI). Prevalence of RHD (and 95% CI) will be calculated for the different participating communities and jurisdictions, stratified by sex and age group, based on proportion of people screened who have a diagnosis of RHD. Prevalence of known RHD will also be estimated by calculating the proportion of people in the community with a diagnosis of RHD entered on the relevant register at completion of the study.

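### The stated 80% power is tied to the number of people enrolled, but the primary test uses each community's whole target population as its denominator, so the power figure does not describe the planned analysis

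*Protocol article*

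**What the plan says.** All references are to the protocol article.

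- **Sample size calculation.** The calculation is said to rest on the primary outcome. The effect is given as "To observe an absolute increase of 2.4% of the target population prescribed secondary prophylaxis, from a baseline prevalence of 4.4% to 6.8" per cent, and "with 95% two-sided significance and 80% power, the sample size required is 1421". The recruitment aim follows directly: "The study will aim to enrol >1500 participants (children and pregnant women) across approximately 10 sites (~150 participants per site").
- **Abstract, Methods and analysis.** The 1500 are the people scanned: "Approximately 1500 children and pregnant women will be screened across high-risk communities in Australia and Timor-Leste over an 18-month period".
- **Setting and population.** "The target population in each community includes children and young people aged 5–20 years and pregnant women". This is a community population, not a list of participants.
- **Quantitative data analysis.** For the primary outcome the numerator comes from clinic and register data, and "the denominator will be based on census population data or health information system population data". Start and end proportions are compared with a two-sided test: "A p value <0.05 will be considered significant". The same section uses enrolled or screened people as the denominator only for secondary results (progress through the cascade of care, and prevalence among those screened).
- **Participation and recruitment.** Scanning is expected to be mainly opportunistic in primary care, with occasional organised screening days.

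The article gives neither the size of the target population nor an expected scanning coverage.

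**The concern.** The sample-size section and the analysis section use different units for the same outcome. A required N of 1421 is set beside an enrolment target, as though enrolling 1500 people supplied the N of the test. In the planned analysis, N at each time point is the number of target-population residents in the participating communities, and recruiting more or fewer people does not alter it. Enrolment affects the result by another route: it caps how many residents can be newly detected, and so the size of the effect.

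What is at stake is how the primary result is read. If the gain is confined to those scanned and coverage is partial, a programme that worked in everyone it reached could give a non-significant primary result. With 80% power on record, that result could be taken as an adequately powered negative. If the gain really is 2.4 points across the whole target population, the quoted power is too low instead, and the yield needed among those scanned goes unstated.

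**Working it through.** **Inputs from the article.** p1 = 0.044, p2 = 0.068, two-sided alpha 0.05, power 80%, required N 1421, planned enrolment 1500.

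**Assumptions.** Coverage c is the share of the target population scanned. The target population is then N = 1500/c at each time point. Unscanned residents do not change. There is no allowance for clustering.

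**Step 1. Reproduce 1421.** For a two-sample comparison with pooled null variance,

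n = [1.96·√(2·p̄·(1−p̄)) + 0.8416·√(p1(1−p1) + p2(1−p2))]² / (p2−p1)², with p̄ = 0.056.

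- 1.96·√0.105728 = 0.6373
- 0.8416·√0.105440 = 0.2733
- (0.9106)² / 0.000576 ≈ 1440

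The unpooled version gives 1437 and the arcsine version 1425. A one-sample test against a fixed 4.4% gives 655, so it does not explain the figure. The stated 1421 is therefore the number of independent people at **each** time point, with no design effect. Power is 79.5% at 1421 and 81.6% at 1500. The arithmetic is sound; the question is which N it applies to.

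**Step 2. Reading A: the 2.4 points is the gain among those scanned.** The whole-population gain is 2.4c points. The net addition is always 0.024 × 1500 = 36 people, and only the denominator grows. Power = Φ{[d√N − 1.96·√(2·p̄·(1−p̄))] / √(p1(1−p1) + p2(1−p2))}, with d = 0.024c and p2 = 0.044 + d.

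Example at c = 50%: N = 3000, p2 = 0.056, p̄ = 0.050. Then 0.012·√3000 = 0.6573; 1.96·√0.095 = 0.6041; (0.6573 − 0.6041)/0.3081 = 0.173; power ≈ 57%.

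**Step 3. Reading B: the 2.4 points is the gain in the whole target population.** Here d = 0.024 whatever c is, and the gain among those scanned must be 2.4/c points.

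Example at c = 50%: 0.024·√3000 = 1.3145; (1.3145 − 0.6373)/0.3247 = 2.086; power ≈ 98%. The gain needed among those scanned is 2.4/0.5 = 4.8 points, or 72 of 1500 people.

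| Coverage c (assumed) | N per time point | A: whole-population gain | A: power | B: power | B: gain needed in those scanned |
|---|---|---|---|---|---|
| 100% | 1500 | 2.4 points | 82% | 82% | 2.4 points |
| 75% | 2000 | 1.8 points | 72% | 91% | 3.2 points |
| 50% | 3000 | 1.2 points | 57% | 98% | 4.8 points |
| 25% | 6000 | 0.6 points | 34% | >99% | 9.6 points |

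The two readings meet near the stated 80% only at full coverage.

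**The case against.** **The effect is worded as a share of the target population.** Taken literally, that is Reading B, and unclustered power is then above 80% whenever the target population exceeds 1500. This stands. A reader might infer from the dilution figures that the study is underpowered, but the article does not support that: it gives no coverage, and its own wording fits the reading in which power is higher. What the literal reading does not do is explain why 1421 is met by counting enrolled people, or say what yield among those scanned it presupposes.

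**A programme that reaches few people should show little population effect.** This also stands. The outcome was chosen to show public health impact, and the Limitations and strengths section accepts that it reflects implementation as a whole. Using the census denominator is not the fault. Quoting a power that belongs to a different denominator is.

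**Much of the interpretive information is already planned.** Penetration is an implementation outcome, numbers starting and stopping prophylaxis in each community are secondary outcomes, and cascade progress among enrolled participants is reported. These would help explain a null result. They do not correct the power statement.

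**This is a condensed article.** Site populations may be in the full protocol. But both relevant sections are printed here and they use different units, so the point is an inconsistency in what is stated, not a missing detail.

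Two further inferences should not be drawn. One is to multiply the 2.4 points by the quoted SPLASH sensitivity. The 6.8% comes from a cited source not at hand, and it cannot be known whether it already reflects imperfect detection. The other is that women scanned while pregnant drop out of the end-of-study denominator. The article does not define that denominator by pregnancy on the end date.

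**Conclusion.** The concern holds in a limited form. The number 1421 is correctly computed for a simple two-sample comparison, but the planned primary test does not take its N from enrolment. The stated 80% fits that test only if about 1500 people are essentially the whole target population, which the article does not say and which mainly opportunistic scanning does not suggest. At 50% coverage, unclustered power could be 57% or 98% depending on whom the 2.4 points describes; at 75% it could be 72% or 91%. These figures rest on assumed coverage, no change among unscanned residents, and independence between people. The conclusion is that the power is misattributed; its direction of error cannot be settled from the article.

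**What to change.** In the sample-size section:

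1. State the target-population size summed over sites and the expected scanning coverage.
2. Say whether 2.4 points is a gain in the whole target population or in those scanned.
3. Restate power on the census or health-system denominator for the implied whole-population gain, over a range of coverage.

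In the analysis section:

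4. Report coverage for each community beside the primary result.
5. If each enrolled person's prescription status before the scan and at study end is captured, add a supportive before/after analysis in enrolled participants. The data-collection section lists commencement of prophylaxis and history of known disease, but does not clearly list both of these status points, so this should be confirmed first.

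The cost is revised wording, a short recalculation and at most one minor extra analysis. The stated power may move in either direction. No extra participants are needed, and the primary outcome and test stay as they are.
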